#### Secondary Implementation Outcomes

##### Secondary Aim 1: To Assess the Effect of Continuous Quality Improvement (Ongoing MS Feedback) in Sustaining the Primary Outcomes

The data structure is identical to that described for the primary effectiveness outcome. To evaluate the outcomes in the sustainment period, including the number of tests administered to young sexual minority men and MS scores, a dichotomous indicator will be added at the agency level to differentiate agencies randomized to continued MS feedback from those randomized to no further intervention. In the model detailed for the primary effectiveness outcome, cross-level interactions will be specified between this condition indicator and the level-2 sustainment phase indicator, along with the level-1 growth term for the sustainment phase. This will test the extent to which changes in outcomes during the sustainment phase differ for agencies receiving ongoing MS feedback versus the control arm. Likewise, the model can be simplified to test for a difference in the average level of MS scores and young sexual minority men tested rather than change over time during this phase.

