## Methods

### Study Design

The YACHT program will be tested using a type 2 implementation-effectiveness hybrid trial with a stepped wedge cluster randomization (Figure 1). The trial comprises variable preimplementation phases (quarterly MS visits), a 12-month implementation phase (MS feedback along with TMI WD strategies and recommendations for improvement), and variable sustainment phase. For the stepped wedge, agencies will be randomly assigned to blocks. The number of assessments will be consistent across blocks, but baseline and sustainment windows will vary by block. The preimplementation phase will provide baseline data over a specified period before the implementation package is delivered. The preimplementation phase for block 1 will last for 12 months, whereas the preimplementation phase for block 7 (last block) will last for 30 months. Subsequently, each block will transition from preimplementation to implementation delivery at a 3-month interval. The implementation phase will last for 12 months and will be delivered to all the agencies within each block. MS visits will continue quarterly to inform implementation. At the end of the 12-month implementation period, the agencies will transition to the sustainment phase. Agencies within each block will be rerandomized to groups marked for either ongoing QM (MS feedback) or no further feedback (observation only). The length of the sustainment phase for block 1 will be of 24 months; for block 7, the sustainment phase will be of 6 months. We will conduct qualitative interviews with clinics’ testing providers and staff after the completion of the implementation and the sustainment phases using a sequential explanatory mixed methods approach. Implementation facilitators at each study site will collect written informed consent from the testing providers and staff before the interviews. Our logic model will guide the interview process (Textbox 1). The study will evaluate whether the YACHT program leads to an increase in HIV testing by comparing the number of young sexual minority men who test for HIV postimplementation versus preimplementation (primary effectiveness outcome). In addition, we will evaluate program implementation based on MS assessments of fidelity to developmentally and culturally responsive evidence-based CTR practices (implementation outcomes).

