#### Group Coaching

Standardized 1-hour virtual coaching sessions (up to 4 per agency) will include a brief interaction to elicit motivation for TMI implementation and then, behavioral skills acquisition based on the lowest ratings received on the most recent MI-CRS and MS assessments. The coaching of each skill will follow the skills acquisition steps of modeling, verbal and behavioral rehearsal, and feedback.

In the sustainment phase, agencies will be randomized to either continue receiving written feedback from the quarterly MS assessments or no additional feedback. Agencies will not have any contact with the TMI coaches during this period; however, agencies may continue to seek TA from FDOH as standard of care.

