#### Analytic Strategy

We will use descriptive and graphical approaches to describe demographic characteristics, evaluate distributional properties, and identify outliers. The primary outcome of this study is the number or rate of HIV tests among young sexual minority men at each of the 42 FDOH-contracted CTR agencies in the 7 Florida EHE counties. The secondary outcome of this study is the mean score changes across MS domains at each of the FDOH-contracted CTR agencies. We will use generalized linear mixed models to evaluate our outcomes under the intention-to-treat analysis framework. Specifically, we will explore the use of the mixed-effects negative binomial model or the mixed-effects Poisson regression model for estimating risk ratio between the treatment and control arms for the testing data, and a mixed-effects model with a normal distribution for the MS data. Time will be included in the model as continuous exposure. Our models will evaluate the difference between the intervention and control arms, adjusting for calendar time and exposure time, which is recommended by Nickless et al [56] to reduce bias in stepped wedge cluster randomized trials. To account for correlation between multiple tests conducted within each agency and heterogeneity between agencies, we will include an agency-specific random effect term. We will also explore the inclusion of a higher order quadratic term for time for better model fit. Akaike information criteria and Bayesian information criteria will inform final model selection. We will calculate the intervention effect after 3, 6, 9, and 12 months of exposure and the time-averaged intervention effect. We will report 95% CI and corresponding *P* values for our parameter estimates. At the conclusion of the 1-year intervention period, agencies will be randomized to continuous quality improvement versus control groups to evaluate sustainment over time. The sustainment period will be 24 months for agencies that receive intervention during the first step and 6 months for agencies that receive intervention during the last step. We will again use mixed-effects regression models to evaluate the difference between continuous quality improvement versus control groups over time.

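### The sustainment model freely estimates a pre-sustainment difference between two randomised arms that are treated alike until then; constraining it to zero would make the average-level contrast modestly more precise

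*Protocol article*

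**What the plan says.** Secondary Aim 1 in the Protocol article compares agencies with and without continued mystery-shopper feedback, for test numbers and for shopper scores. It extends the model for the primary effectiveness outcome, which spans all phases:

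- **Arm term:** "a dichotomous indicator will be added at the agency level to differentiate agencies randomized to continued MS feedback".
- **Step term:** "cross-level interactions will be specified between this condition indicator and the level-2 sustainment phase indicator".
- **Growth term:** the same indicator is interacted "along with the level-1 growth term for the sustainment phase".
- **Simplified version:** "Likewise, the model can be simplified to test for a difference in the average level of MS scores", with the number of young men tested treated in the same way.
- **Correlation:** under Analytic Strategy, "we will include an agency-specific random effect term".

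The arms are formed by chance: under Group Coaching, "agencies will be randomized to either continue receiving written feedback from the quarterly MS assessments or no additional feedback". Before that all agencies are on the same path: under Study Design, "The implementation phase will last for 12 months and will be delivered to all the agencies within each block", and quarterly shopper visits run throughout. The Results section dates the feedback list to April 18, 2023, before the first shopper visit on June 1, 2023.

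**The concern.** An indicator defined at agency level acts in every quarter. Once its sustainment interactions are in the model, its own coefficient is the arm difference over the preimplementation and implementation quarters. The sustainment arm effect is then read as a departure from that estimate, that is, as a difference in differences.

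Randomisation and identical handling up to sustainment make the expected earlier difference zero, so the data are used to estimate something the design already supplies. The sampling error of that estimate is carried into the arm effect. What is at stake is precision in a secondary comparison of about 21 with 21 agencies, where the last block contributes only two sustainment quarters.

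**Working it through.** **No stated figure to reproduce.** The article gives no power, effect size, ICC or standard error for this comparison. The 36- and 30-agency statements come without inputs and do not concern it.

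**Inputs from the Protocol article**
- 42 agencies in 7 blocks of 6 (Study Design).
- Preimplementation lasts 12 months (block 1) to 30 months (block 7), implementation 12 months, sustainment 24 down to 6 months. Check: 12 + 12 + 24 = 30 + 12 + 6 = 48 months, or 16 quarters in every block, with 8, 7, 6, 5, 4, 3 and 2 sustainment quarters.
- Agency random effect (Analytic Strategy).
- Each quarterly shopper score pools 2 visits, so a low ICC is plausible for scores, though not documented.

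**Assumptions:** equal arms (3:3 in each block), and an ICC range for the quarterly agency value.

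**Closed form for one agency.** Let t2 be the between-agency variance, s2 the within-agency quarterly variance, m0 the number of earlier quarters and m1 the number of sustainment quarters.
- Free arm term: s2/m0 + s2/m1.
- Arm term fixed at zero: s2/m1 + t2(s2/m0)/(t2 + s2/m0).

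The second is always smaller. At the middle of the calendar (m0 = 11, m1 = 5) with ICC 0.2 (t2 = 0.2, s2 = 0.8):
- free: 0.8/11 + 0.8/5 = 0.0727 + 0.1600 = 0.2327
- fixed: 0.1600 + 0.2 × 0.0727/0.2727 = 0.1600 + 0.0533 = 0.2133
- ratio: 0.2327/0.2133 = 1.09

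**Full layout.** The variance of the arm terms was computed for all 42 agencies and 16 quarters, with quarter effects, implementation, sustainment and growth terms and a random-intercept fit. The true agency correlation was either constant or decaying geometrically by 0.95 or 0.90 per quarter. Entries are variance with the free arm term divided by variance with it fixed at zero, for the average-level contrast (no arm-by-growth term):

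| ICC | constant | decay 0.95 | decay 0.90 |
|---|---|---|---|
| 0.2 | 1.10 | 1.17 | 1.22 |
| 0.3 | 1.06 | 1.13 | 1.17 |
| 0.5 | 1.03 | 1.08 | 1.12 |
| 0.9 | 1.00 | 1.03 | 1.06 |

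If only 30% of the agency variance decays (by 0.8 per quarter), the ratios lie between the first two columns: 1.14, 1.10 and 1.06 at ICC 0.2, 0.3 and 0.5. Quadratic time instead of quarter effects changes the ratios by no more than 0.003.

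**With the arm-by-growth interaction also in the model** (growth counted from zero at the start of sustainment):

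| ICC | step, constant | step, decay 0.90 | growth difference |
|---|---|---|---|
| 0.2 | 1.04 | 1.09 | 1.00 |
| 0.3 | 1.03 | 1.07 | 1.00 |
| 0.5 | 1.01 | 1.05 | 1.00 |

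Counting growth from one instead of zero lowers the step ratios to 1.03, 1.02 and 1.01 (constant) and 1.05, 1.04 and 1.03 (decay 0.90).

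**On the scale of standard error and power.** A ratio of 1.10 means a standard error larger by √1.10 − 1 = 4.9%. A contrast with 80% power at two-sided 5% under the free model at ICC 0.2 and constant correlation would have 83.5% once the term is dropped: 2.80 × √1.097 − 1.96 = 0.97, whose normal probability is 0.835.

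**The case against.** The strongest defence is that nothing in the specified model is wrong. A main effect with its interactions is standard and well formed, and the estimate is unbiased. A reader might infer from the free arm term that the sustainment comparison is biased or invalid. The documents do not support that; the point concerns efficiency only.

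A second objection concerns size. A reader might infer a 10 to 20% loss of variance for Aim 1 as a whole, or a loss worth several agencies. That does not hold either. The larger figures belong to the simplified average-level test of shopper scores, at low ICC or with fading correlation. In the model as first specified, with the growth interaction, the step term loses a few percent and the growth difference essentially nothing. Nor can one say that this is the trial's least precise randomised contrast, since no precision is stated for any contrast.

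Third, the constraint is not wholly free of cost. The free term removes a stable earlier arm difference whatever its cause; the constrained model removes it only partly, through the random effect. The feedback list predates block 1's sustainment (June 1, 2025) by more than two years, and the article does not say that it is hidden from the facilitators who tailor each site's package. This stands as a small downside, which a sensitivity analysis addresses. Chance imbalance under simple randomisation is not in itself a reason to keep the term, because the retained earlier quarters and the agency effect adjust for each agency's own history.

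**Conclusion.** The point holds as a cheap improvement and not as an error. The Aim 1 model estimates an arm difference that the design makes zero in expectation, and on this layout with a random-intercept fit fixing it at zero is never less precise. For the average-level contrast the avoidable excess variance is:

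- **Shopper scores, ICC 0.2 to 0.5:** about 3 to 10% under constant correlation, about 8 to 22% under geometric decay.
- **Test counts, ICC near 0.9:** 0 to 6%.

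With the growth interaction in the model the excess at ICC 0.2 to 0.5 is about 1 to 9% for the step term and essentially none for the growth difference.

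These figures rest on assumed ICCs and correlation patterns, since the article gives none, and on equal arms within blocks. The direction does not depend on the ICC, but it does require that the arms are handled alike until sustainment.

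**What to change.** In the Aim 1 model, and above all in its average-level version for shopper scores:

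1. Keep all preimplementation and implementation quarters, with one common mean for both arms.
2. Drop the uninteracted feedback indicator. Let arm enter only through its sustainment-phase and sustainment-growth terms.
3. Report the model with the free arm term as a sensitivity analysis.
4. Confirm that facilitators do not know the feedback assignment before an agency's sustainment phase begins.

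Comparing the arms on sustainment quarters alone is not a substitute. In the closed-form example at ICC 0.2 its variance is 0.2 + 0.16 = 0.36, or 0.36/0.2327 = 1.55 times that of the free model.

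The cost is a change of wording in the analysis plan plus the confirmation in step 4. No further data or agencies are needed. Data collection runs to May 31, 2027, so the change can still be fixed in advance of the sustainment analysis.

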##### Secondary Aim 2: To Use Mixed Methods Based on the EPIS Framework to Understand Barriers to and Facilitators of Successful Implementation and Sustainment of Youth-Specific EBPs

Up to 5 testing providers per agency will be interviewed immediately after the Implementation and Sustainment periods using the EPIS-based HIV interviews developed in preliminary studies. Accordingly, the interviews (45-60 min) will focus on the inner and outer context factors influencing the implementation of RRC, PrEP referral, and TMI; utility of and adherence to the YACHT strategies; and bridging and innovation factors to consider for future scalability and sustainment. We will use rapid content analysis as recommended to produce actionable information for planners and decision makers [56,57] by first summarizing individual interviews using a rapid feedback template of EPIS constructs and then consolidating the summaries by the main EPIS factors. Next, we will adapt the innovation profile approach [58] originally developed for classroom research. This approach results in a multidimensional rubric to classify where an organization is in the process of developing its capacity to engage in a particular set of activities; in this case, it is the integration of EBPs into routine service provision. The dimensions and subdimensions of the matrix we develop, as well as descriptions of the behavioral indicators of exemplary, intermediate, emerging, and low capacity to integrate EBPs will be derived from aggregating the data produced during content analysis at the agency level. These data will be integrated with the quantitative fidelity and the outcomes data using a sequential explanatory design where qualitative findings are used to help explain variability in fidelity and outcomes [59].

## Results

The study was funded on August 4, 2022. A simple randomization scheme was generated using SAS (version 9.4; SAS Institute) to assign agencies to receive feedback versus no feedback during the sustainment phase on April 18, 2023. MS visits were initiated on June 1, 2023. As of June 2024, 194 MS visits have taken place at 42 sites. In addition, 4 sites from the first block and 1 site from the second block have engaged with the study. At baseline assessment, sites exhibited the lowest competencies in relationship context, counseling session, and safer sex education, and the highest competency in the privacy and confidentiality domain.

The exploration phase is projected to last from June 1, 2023, to March 31, 2024 (10 months), for block 1 and until September 30, 2025, for block 7 (28 months), with the other blocks staggered every 3 months. The preparation phase for block 1 started on April 1, 2024, and is projected to take up to 2 months for each block. The implementation phase will last for 1 year and started on June 1, 2024, for block 1 and will begin on December 1, 2025, for block 7, with other blocks staggered every 3 months. Finally, the sustainment phase will start on June 1, 2025, for block 1 and last for 2 years. For block 7, it will start on December 1, 2026, and continue for 6 months. Data collection will be completed by May 31, 2027.

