### Goal

In this manuscript, we present the protocol to test the effectiveness of the YACHT implementation package to improve the fidelity to the “diagnose” and “prevent” EBPs in CTR sites in Florida’s 7 EHE jurisdictions (Multimedia Appendix 1). Guided by the EPIS framework, we will examine both effectiveness (number of HIV tests conducted among young sexual minority men) and implementation (EBP fidelity) outcomes. After intervention implementation, a second randomization will be conducted to test whether the implementation of ongoing QM strategies (MS feedback reports) serves as a sustainment strategy. Our study also contains a qualitative component based on the EPIS framework to further understand the context of implementation and sustainment (sequential explanatory mixed methods) [46].

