The study will use a multicomponent implementation strategy based on the EPIS framework (Figure 2). MS assessments will be used for quality monitoring, and WD strategies will include TMI training and evidence-based TA at HIV-testing sites. All testing sites in Florida EHE counties that tested at least 24 young sexual minority men aged between 18 and 29 years in 2021 will be invited to participate. Participating sites (N=42) will be randomized to receive the YACHT program in 7 blocks of 6, following a stepped wedge design (Textbox 1). They will receive TMI training for RRC and PrEP referrals and evidence-based TA for their identified areas of need, based on MS feedback. Finally, we will use the EPIS framework to understand the barriers to and facilitators of program implementation and sustainment.

This study design will accommodate real-world constraints and provide strong evidence for evaluating the research aims. It is carefully configured to optimize statistical power and will afford numerous and increasingly well-known benefits, including 2 comparisons for assessing the effect of the implementation package (ie, including inter- and intracluster comparisons for assessing the effect of the implementation package), evaluation and control of outer context factors, substantial rigor and power relative to quasi-experimental alternatives, and superior feasibility and power relative to alternative randomized designs. Institutional review board approval from the Florida State University was obtained on December 12, 2022.

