## Discussion

### Principal Findings

We hypothesize that the YACHT implementation package will contribute to increasing the number of HIV tests conducted among young sexual minority men and improving the developmentally and culturally responsive delivery of EBPs by participating sites in Florida’s 7 EHE jurisdictions. An important innovation of our proposed approach is using the services of MSs who are young sexual minority men to identify areas of strength and improvement in the delivery of CTR services for young sexual minority men at participating sites. The proposed design guided by the EPIS framework, a type 2 implementation-effectiveness hybrid trial with a stepped wedge cluster randomization, will allow us to examine both effectiveness outcomes (number of HIV tests on young sexual minority men) and implementation outcomes (EBP fidelity). The second randomization conducted after intervention implementation will test whether the delivery of ongoing QM (MS feedback reports) serves as a sustainment strategy. The qualitative component will advance our understanding of the context of implementation and sustainment.

MS visits started on June 1, 2023. We have learned that recruitment of MSs is challenging and often requires more resources than originally allocated. Recruitment via dating apps such as Jack’d has been most successful but requires an advertising budget that is more extensive than simply posting on social media or posting flyers in local universities and cafes. Interest in serving as an MS varies by geographic location. Scheduling and MS retention can be demanding and often requires extensive efforts from research assistants. The current compensation structure for MSs merits further examination. Most MSs are neither university employees nor study participants but consultants. We pay them on a per visit basis as has been done in previous work with young sexual minority men [53]. However, timeliness of the payment per University processes prevents immediate payment upon visit completion, which may also deter engagement of MSs.

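### The sustainment arms are reported as a simple randomization list drawn in April 2023, but the design describes rerandomization within each block after implementation; an unstratified list can leave arms unbalanced across blocks

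*Protocol article*

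**What the plan says.** Four places in the protocol article put the second randomization at or after the end of implementation.

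- Goal: "After intervention implementation, a second randomization will be conducted".
- Study Design, describing the move into sustainment after 12 months of implementation: "Agencies within each block will be rerandomized to groups marked for either ongoing QM (MS feedback) or no further feedback (observation only". This is the only place that makes the block the unit within which agencies are rerandomized.
- Analytic Strategy: "At the conclusion of the 1-year intervention period, agencies will be randomized to continuous quality improvement versus control groups".
- Principal Findings: "The second randomization conducted after intervention implementation will test whether the delivery of ongoing QM (MS feedback reports) serves as a sustainment strategy".

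Results reports what was done. The method is given as "A simple randomization scheme was generated using SAS (version 9.4; SAS Institute) to assign agencies to receive feedback versus no feedback", and the purpose and date as "to assign agencies to receive feedback versus no feedback during the sustainment phase on April 18, 2023". It mentions no stratification by block.

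Two design facts give block its importance. Sites "will be randomized to receive the YACHT program in 7 blocks of 6, following a stepped wedge design", and the follow-up available for the second comparison depends on the block: "The length of the sustainment phase for block 1 will be of 24 months; for block 7, the sustainment phase will be of 6 months".

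The model under Secondary Aim 1 adds an agency-level feedback indicator and its interactions with the sustainment phase and its growth term. It names no block term. It also allows a simplified comparison of average level over the phase.

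**The concern.** The article gives two accounts of one randomization, and they differ in timing and, on their face, in method. This is more than detail left to a fuller document: the article states the method, date and purpose of the allocation, and these disagree with its own design section.

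The method matters because block determines both when an agency's sustainment period falls and how long it lasts. Balanced allocation inside each block would keep the feedback contrast clear of both. A single simple list over all 42 agencies would not: one arm could by chance hold more early-block agencies, with longer and earlier sustainment. The feedback contrast is the only randomized comparison behind Secondary Aim 1. The timing matters less, but an early list fixes the arms before it is known which agencies close or drop out, so balance on the list may not last until sustainment.

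**Working it through.** **Inputs from the article.** 42 agencies in 7 blocks of 6 (Study Design). Steps of 3 months; sustainment of 24 months for block 1 and 6 for block 7 (Study Design, Analytic Strategy, Results). List dated April 18, 2023; first shopper visits June 1, 2023; block 1 implementation starts June 1, 2024; sustainment starts June 1, 2025 (block 1) and December 1, 2026 (block 7) (Results).

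**Assumption.** The article gives no allocation ratio. I take 1:1, first as independent coin flips, then as a fixed 21:21 split that ignores block.

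**Reproducing the stated lengths.** Length for block k = 24 − 3(k − 1), which gives 24, 21, 18, 15, 12, 9 and 6 months. This matches the stated figures for the first and last blocks.

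**Timing.** From April 18, 2023 it is 44 days to the first shopper visits, about 13 months to the start of block 1 implementation, about 25 months to block 1 sustainment and about 43 months to block 7 sustainment. The list therefore precedes implementation in every block.

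**Block splits under independent 1:1 assignment.** The number in the feedback arm in a block is binomial(6, 0.5).

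- Exactly 3:3: C(6,3)/64 = 20/64 = 0.3125, so a block misses 3:3 with probability 0.6875. This counts 4:2 as a miss.
- All seven blocks 3:3: 0.3125^7 = 0.0003.
- 5:1 or 6:0 in a given block: 2 × (1 + 6)/64 = 14/64 = 0.21875. At least one of seven: 1 − (50/64)^7 = 0.82.
- 6:0 in a given block: 2/64 = 0.03125. At least one of seven: 1 − (62/64)^7 = 0.20.

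**Difference between arms in mean sustainment length.** The block lengths deviate from their mean of 15 by ±9, ±6, ±3 and 0, so their variance over the 42 agencies is 2 × (81 + 36 + 9)/7 = 36. For a fixed 21:21 split the variance of the difference in means is 36 × (42/41) × (2/21) = 3.51, so the SD is 1.87 months. Simulation of 200,000 lists gives the same value for 21:21 and 1.90 for coin flips. The simulated probabilities are:

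| List | Any block 5:1 or worse | Any block 6:0 | Difference ≥ 2 months | ≥ 3 months | ≥ 4 months |
|---|---|---|---|---|---|
| Coin flips | 0.82 | 0.20 | 0.32 | 0.11 | 0.04 |
| 21:21, not stratified | 0.72 | 0.13 | 0.32 | 0.11 | 0.04 |
| 3:3 within each block | 0 | 0 | 0 | 0 | 0 |

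**The case against.** The case on the other side has several parts.

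- *The word simple may be loose, or the sentence may mix up the step allocation with the sustainment allocation.* Possible. The article does not settle it, so the imbalance figures are conditional on an unstratified list. The conflict in timing stands either way.
- *Only Study Design mentions blocks, and nothing promises 3:3.* Correct. Coin flips run inside each block would satisfy that sentence and give the same probabilities. The figures therefore measure the gap between an unrestricted list and a balanced within-block one, not the gap between two stated procedures.
- *The model already adjusts for time.* Secondary Aim 1 builds on the primary model, and Analytic Strategy adjusts that model for calendar and exposure time. Block start is calendar time minus time since start, so these terms can carry a linear block effect if exposure time keeps counting into sustainment, which the article does not say. Part of any imbalance may be absorbed this way.
- *The imbalance in length is usually modest.* True: the SD is 1.9 months, and a gap of 4 months or more has probability 4%.

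Three stronger readings are tempting, and the article does not support them. A reader might infer that the contrast is biased; a simple random list is unbiased in expectation, so the risk is chance imbalance. A reader might infer that facilitators knew the arms while delivering implementation; the article says only that a scheme was generated, and an early list is no fault if it is concealed. A reader might count the inclusion of agencies that never engage as a defect; Attrition and Missing Data keeps clusters as allocated whether or not they participate, so this follows the stated intention-to-treat rule.

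**Conclusion.** The inconsistency is real and needs correcting. Results dates the sustainment allocation to April 18, 2023, whereas four other places put it after implementation or at its end. Results calls the scheme simple, whereas Study Design describes rerandomization within block. A reader cannot tell which procedure produced the arms.

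If the list was not stratified by block, some imbalance across blocks is close to certain and a marked one in at least one block is likely, at the probabilities worked out above. Those rest on an assumed 1:1 ratio. The coin-flip and 21:21 versions agree on the difference in sustainment length and differ moderately on block splits. The consequence is lost balance and precision in the feedback comparison, partly offset by the time adjustment. The primary stepped-wedge contrast is not affected.

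**What to change.** State which procedure generated the sustainment arms, when, and whether it was stratified by block. Reconcile Goal, Study Design, Analytic Strategy, Results and Principal Findings accordingly. Then:

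1. **If the list was unstratified and can be replaced:** redraw a balanced allocation within block (3:3 where all six agencies remain) for each block not yet in sustainment, and conceal it until that block's implementation phase ends. On the article's schedule block 1 enters sustainment on June 1, 2025, after the November 2024 publication, so at publication this was open for all seven blocks. The cost is one short program run per block and an amendment sentence; no sites or data are added.
2. **If the list stands:** correct the design text, report the table of arm by block, and include block as a fixed effect in the Secondary Aim 1 model. With 7 blocks this costs 6 degrees of freedom among 42 agencies. A block main effect adjusts the comparison of average level directly. For the test of change during sustainment, a sensitivity fit with block by sustainment phase would show whether imbalance is driving the result.

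If only some blocks can be redrawn, use the first option for those and keep the block term for all.
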